### 2.5. Protocol

At the initial visit, the study team will evaluate potential participants to determine if they meet the inclusion or exclusion criteria. The investigators will provide detailed explanations of the study and ensure that informed consent is obtained by presenting consent forms and discussing the study with the participants. This stage involves obtaining documented approval from all participants. Subsequently, individuals with SCI fill out a guided survey and submit it to a medical professional for medical status and assess the responses. Prior to randomization, qualified assessors will evaluate the outcome variables for each participant.

### 2.6. Program

The training program consists of 1 h classes conducted biweekly over a period of 2 months, as detailed in Table 1. Participants in the exercise group will have access to the VRFT devices not only during the biweekly classes but also at home throughout the trial period. This will allow the participants to engage in additional sessions as desired.

The rehabilitation protocol for spinal cord injury comprised cardiovascular and strength training exercises, as well as practical exercises focusing on the extremities and core. Furthermore, specialized programs were designed considering the goals and the type of exercise, time, frequency, duration, and intensity, adhering to the guidelines of the American College of Sports Medicine. The intervention program will incorporate the use of the Ringfit Adventure (RA) game for the Nintendo Switch (NS). (Figure 2). RA, a fitness program for the Nintendo, utilizes semi-immersive technology.

Individuals with SCI will require an NS system, a Ring-Con (RC) (a flexible exercise ring held by the participant), a Bluetooth operator (attached to the RC and the other fastened to a leg strap on the participant’s quadriceps), and a monitor for this training class. The class is scheduled twice a week over eight weeks. Each class will be 1 h long, consisting of 10 min for warming up, 10 min for cooling down, and 40 min dedicated to the primary exercise session. RA is an action role-playing fitness game that advances the storyline through the player’s physical activities, which directly influence the character’s on-screen movements. These exercises are performed with the aid of the RC and thigh band [30]. The RC contains highly accurate pressure and tension detectors that capture and translate the individual’s movements [31]. Additionally, the Bluetooth operator features an infrared motion sensor capable of tracking the participant’s pulse rate [32]. RA has the capability to assess the ideal intensity of physical activities tailored to each individual and modify it according to biological signals either lowering or raising the activity level. In the first class, the virtual coach determines the intensity of physical activities and then progressively modifies them according to feedback from later sessions. The research staff will consistently supervise individuals in the exercise group, who will encourage participants to sustain the 16-session class at 60% to 80% of the individual’s baseline and the highest heart rate. Participants will be guided to keep their exertion within the range of 4 to 8 on the modified Borg CR10 rating of perceived exertion scale, which translates to a perception of effort from ‘moderate’ to ‘vigorous’ [33]. Participants in the comparison group will adhere to their normal routines and will not receive any specific intervention throughout the study.

### 2.7. Measures

Individuals with SCI will perform initial assessments and subsequent evaluations after 16 classes, utilizing the assessment outlined (Table 2). A custom-designed questionnaire will be used to gather descriptive and sociodemographic information. Outcomes will measure muscle function (including grip strength), cardiopulmonary fitness (including VO_2_peak and respiratory function), body composition (through full-body DXA scanning and bioimpedance measurement), and physical performance (functional reach test) to determine overall physical fitness. The primary outcome of this study is physical fitness factors, specifically muscle strength, cardiopulmonary fitness, body composition, and physical performance. Secondary outcomes include psychological factors such as quality of life. Individuals with SCI will perform initial assessments and subsequent evaluations after 16 classes utilizing the assessment outlined in Table 2. Incorporating these spinal cord injury-specific measures will provide a thorough evaluation of the participants’ rehabilitation progress and functional gains following the training.

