#### 2.7.1. Muscle Function

The upper extremity muscle strength assessment will be conducted by measuring the grip strength of each participant using a hand dynamometer (TKK-5401; Takei Scientific Instruments, Tokyo, Japan). Participants will be positioned with their shoulders gently drawn inward and in a neutral rotation, the elbow at a 90-degree angle, and the forearm and wrist maintained in a neutral posture. Each hand will undergo three testing sessions, preceded by a practice trial. The mean value of the three recorded measurements will be utilized for each hand [34].

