#### 2.7.2. Cardiopulmonary Fitness

A progressive peak oxygen uptake test will be administered to all participants to assess their cardiopulmonary fitness. Using an arm crank ergometer (Lode), participants will start at a workload of 10 W for 2 min. The workload will increase by 10 W every 2 min until the participant reaches voluntary exhaustion. The peak aerobic power will be defined as the VO_2_ measurement when the participant can no longer maintain a cadence of 60 rotations per minute (RPM) [35]. A nose-and-mouth facemask will be used to collect expired air, which will be analyzed for oxygen uptake and carbon dioxide output every 10 s using a gas exchange system (K5 system, Cosmed, Rome, Italy). A Polar heart rate monitor will continuously monitor the heart rate, and the rating of perceived exertion (RPE) will be recorded using the Borg scale.

The assessment of respiratory function will be conducted using a digital spirometer (Pony FX, COSMED, Rome, Italy) [36]. Participants will receive thorough explanations and demonstrations of the test procedures to ensure accurate measurements, after which the respiratory function tests will be conducted [37]. This study will measure parameters such as forced vital capacity (FVC), vital capacity (VC), peak expiratory flow (PEF), forced expiratory volume in 1 s (FEV1), inspiratory reserve volume (IRV), expiratory reserve volume (ERV), and inspiratory capacity (IC). The evaluation of respiratory muscle strength will involve assessing the maximum expiratory pressure (MEP) and maximum inspiratory pressure (MIP) using the Pony FX device (COSMED, Rome, Italy) [37].

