### 2.9. Data Collection Methods and Analysis

Outcome measures will be collected before and after the 16 intervention sessions, excluding the sociodemographic and descriptive information.

The sample size determination was based on prior research findings [34]. A power analysis was conducted using G*Power software (version 3.1.2.) [39]. The analysis used an effect size of 0.5 for the outcomes, a power level of 80% (type II error of 0.2), and a significance level of 0.05. We calculated that 29 individuals per group would be required to achieve the necessary statistical power. Therefore, we plan to enroll 30 individuals per group, resulting in a total of 120 participants across the four groups. This calculation ensures sufficient power to detect meaningful differences between the intervention and control groups.

We will assess participant characteristics and baseline comparisons to assess the comparability between the exercise and control groups. A table will be provided to display the characteristics of individuals assigned by the group. Percentages and frequencies will be used to present categorical elements, and time intervals along with continuous elements will be summarized using medians, standard deviations, means, and interquartile ranges. This procedure secures the baseline equivalence between the groups.

An intention-to-treat framework will be employed for our statistical analysis. Kolmogorov–Smirnov analysis will be used to assess the normality of the dependent variables for the outcomes. The responsible variables will be characterized based on their distribution, utilizing either medians and interquartile ranges or means and standard deviations. To achieve the objective, hypothesis tests will be conducted for each outcome, positing that the exercise group will have superior outcomes compared to the control group. All estimates will be accompanied by intervals with 95% confidence level. Student’s *t*-test will be applied for independent samples that follow a normal distribution, while the Mann–Whitney U test will be utilized for data that do not conform to a normal distribution.

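### The primary outcome is four whole fitness domains with no named variable, so no result is designated to decide the trial and the 5% error rate does not cover its conclusion

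*Protocol article*

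**What the plan says.** Section 2.7 (Measures) defines the primary outcome at domain level: "The primary outcome of this study is physical fitness factors, specifically muscle strength, cardiopulmonary fitness, body composition, and physical performance". Secondary outcomes are described as psychological factors such as quality of life, so every physical measure falls on the primary side.

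The subsections fill the domains with separate variables. Grip strength is kept separately by hand: "The mean value of the three recorded measurements will be utilized for each hand". Peak oxygen uptake is joined by an open spirometry list ("This study will measure parameters such as forced vital capacity (FVC), vital capacity (VC), peak expiratory flow (PEF" and four more) and two respiratory pressures. Functional reach stands for physical performance. Body composition has DXA lean and fat mass by body region, and four bioimpedance indices.

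Section 2.9 states the testing rule: "hypothesis tests will be conducted for each outcome, positing that the exercise group will have superior outcomes compared to the control group". The test is a t-test or Mann–Whitney U test. A threshold appears only in the sample-size sentence: "a power level of 80% (type II error of 0.2), and a significance level of 0.05". It is matched by "All estimates will be accompanied by intervals with 95% confidence level". The effect size is equally general: "The analysis used an effect size of 0.5 for the outcomes".

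**The concern.** A primary outcome has to be a variable at a timepoint. Otherwise nobody can say in advance which result would make the trial positive. Here the primary outcome is a set of domains, each domain except physical performance holds several variables, and the rule is a separate superiority test for each outcome. As written, efficacy could be claimed on whichever primary variable crosses 0.05.

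Two things are at stake. The 5% error rate used in planning does not describe the trial's conclusion. And the statement in section 2.9 that power is sufficient to detect meaningful differences cannot be tied to any endpoint.

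**Working it through.** **Inputs.** Primary domains: 4 (section 2.7). Level 0.05, power 80%, effect size 0.5 (section 2.9; read as Cohen's d). Enrolment 120 with 1:1 allocation (sections 2.9 and 2.3), taken as 60 per arm pooled over sites. Sidedness is not stated: the hypothesis is directional and the intervals are 95%. I assume two-sided 0.05 tests. Correlations between outcomes are not given, so a range is assumed.

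**The plan's own figure.** The plan states 29 per group. A two-sided two-sample t-test at d = 0.5, level 0.05 and 80% power needs 64 per group (one-sided 51). With 29 per group, two-sided power is 46%. The stated figure does not reproduce for the planned comparison. That is a separate matter and nothing below depends on it. The plan states no familywise error rate to reproduce.

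**Counting listed variables.**

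| Measure | Section | Variables |
|---|---|---|
| Grip, each hand | 2.7.1 | 2 |
| Peak oxygen uptake | 2.7.2 | 1 |
| FVC, VC, PEF, FEV1, IRV, ERV, IC | 2.7.2 | 7 |
| MEP, MIP | 2.7.2 | 2 |
| Functional reach | 2.7.3 | 1 |
| DXA lean and fat mass | 2.7.4 | 2 (more by region) |
| Bioimpedance: BMI, % fat, muscle mass, weight | 2.7.4 | 4 |

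Sum: 2 + 1 + 7 + 2 + 1 + 2 + 4 = 19.

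**Error rate if independent.** P(at least one p<0.05) = 1 − 0.95^m. For m = 19: 1 − 0.95^19 = 0.623. For m = 4: 1 − 0.95^4 = 0.185. Favouring the training only: 1 − 0.975^19 = 0.382 and 1 − 0.975^4 = 0.096.

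**Error rate if correlated.** Let each test statistic be Z_j = √ρ·G + √(1−ρ)·E_j, with G and E_j independent standard normal, and c = 1.96. Then

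P(any) = 1 − ∫ φ(g)·[Φ((c − √ρ·g)/√(1−ρ)) − Φ((−c − √ρ·g)/√(1−ρ))]^m dg.

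For the favouring direction, drop the second Φ term.

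| Assumed ρ | 19 tests, either direction | 19 tests, favouring VRFT | 4 tests, either direction | 4 tests, favouring VRFT |
|---|---|---|---|---|
| 0 | 62.3% | 38.2% | 18.5% | 9.6% |
| 0.3 | 52.5% | 27.2% | 17.4% | 8.7% |
| 0.5 | 40.9% | 20.5% | 15.6% | 7.8% |
| 0.7 | 28.3% | 14.2% | 13.0% | 6.5% |
| 0.9 | 15.3% | 7.7% | – | – |

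A block structure gives similar values. With correlation 0.7 within and 0.3 between domains, 19 tests give 40% in either direction and 20% favouring the training. If the tests were one-sided at 0.05, the favouring-direction rate for 19 tests at common correlation 0.3, 0.5, 0.7 and 0.9 would be 44%, 33%, 24% and 14%.

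**Power under the remedies** (d = 0.5, 60 per arm, two-sided t-test). One primary at 0.05: 78%. First Holm step with four primaries, 0.05/4 = 0.0125: 58%. With ANCOVA and an assumed baseline correlation of 0.7, the standardised effect becomes 0.5/√(1 − 0.7²) = 0.70, and power at 0.0125 is about 90%.

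**The case against.** Several stronger readings are tempting, and the text does not carry them.

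- *A false-positive primary result is likely.* Only independence and a correlation of 0.3 put the either-direction rate above one half. Independence is implausible for FVC and VC, BMI and weight, DXA lean mass and bioimpedance muscle mass, or the two hands. Because the hypothesis is directional, the error that matters most is the one favouring the training, which is smaller.
- *The plan states 19 primary tests, each at 0.05.* It does not. Nineteen is a count of listed variables, and "each outcome" in section 2.9 may mean domains. BMI and weight also appear in Table 2 as descriptive data. The 0.05 stands in the sample-size sentence; its use for each test is a reasonable inference from the 95% intervals and the absence of any other level.
- *Four tests carry a 13–19% chance of a false efficacy claim.* That is the either-direction rate; favouring the training it is about 7–10%.
- *The missing multiplicity rule is itself the error.* Such a rule could sit in an analysis plan that is not shown, so its absence alone is no finding.

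It can also be said that this is a pilot, concerned with safety and feasibility (Abstract) and meant to inform a larger study (Discussion). That softens how much rests on one p-value. It does not remove the problem, because section 2.9 claims sufficient power and plans superiority tests, and the Discussion and Conclusions speak of efficacy.

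What stands after all this is the definition itself. The protocol positively states a primary outcome that is not a variable. Choosing the variable belongs in the protocol, because the sample size rests on it.

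**Conclusion.** The point holds in this form: four domains are called the primary outcome, no variable is named, and tests for each outcome are planned with one undivided 0.05 and one unattached effect size. The 5% error rate therefore does not apply to the trial's conclusion.

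The inflation is material, but its size depends on assumptions. With 19 variables the either-direction rate is roughly 3 to 12 times nominal (15% to 62%). Against the 2.5% that one two-sided test would give in the favourable direction, it is again roughly 3 to 15 times (8% to 38%). With one variable per domain it is more modest. All these figures assume no true effect on any variable, two-sided 0.05 tests, and correlations that the documents do not give. The defect does not depend on where in the range the truth lies.

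**What to change.** Before unblinded data are seen, name one primary variable at the post-intervention assessment, as a between-arm comparison at two-sided 0.05. The choice is the sponsor's; peak oxygen uptake is only an example, and nothing in the text ranks it first. Tie the effect size and sample-size statement to that variable. Report all other variables as secondary estimates with 95% confidence intervals and no claim of efficacy.

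If the four domains must stay primary, name one variable in each now and test them by Holm at overall 0.05.

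The cost is a change of wording in the protocol and the registration; no new data are needed. The downside is that fewer variables can support a primary claim. At d = 0.5 and 60 per arm, power is 78% for a single primary and 58% at the first Holm step. The second figure rises to about 90% only if the analysis is changed to ANCOVA, which section 2.9 does not plan, and the baseline correlation is 0.7, which is an assumption.

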#### 2.7.1. Muscle Function

The upper extremity muscle strength assessment will be conducted by measuring the grip strength of each participant using a hand dynamometer (TKK-5401; Takei Scientific Instruments, Tokyo, Japan). Participants will be positioned with their shoulders gently drawn inward and in a neutral rotation, the elbow at a 90-degree angle, and the forearm and wrist maintained in a neutral posture. Each hand will undergo three testing sessions, preceded by a practice trial. The mean value of the three recorded measurements will be utilized for each hand [34].

#### 2.7.2. Cardiopulmonary Fitness

A progressive peak oxygen uptake test will be administered to all participants to assess their cardiopulmonary fitness. Using an arm crank ergometer (Lode), participants will start at a workload of 10 W for 2 min. The workload will increase by 10 W every 2 min until the participant reaches voluntary exhaustion. The peak aerobic power will be defined as the VO_2_ measurement when the participant can no longer maintain a cadence of 60 rotations per minute (RPM) [35]. A nose-and-mouth facemask will be used to collect expired air, which will be analyzed for oxygen uptake and carbon dioxide output every 10 s using a gas exchange system (K5 system, Cosmed, Rome, Italy). A Polar heart rate monitor will continuously monitor the heart rate, and the rating of perceived exertion (RPE) will be recorded using the Borg scale.

The assessment of respiratory function will be conducted using a digital spirometer (Pony FX, COSMED, Rome, Italy) [36]. Participants will receive thorough explanations and demonstrations of the test procedures to ensure accurate measurements, after which the respiratory function tests will be conducted [37]. This study will measure parameters such as forced vital capacity (FVC), vital capacity (VC), peak expiratory flow (PEF), forced expiratory volume in 1 s (FEV1), inspiratory reserve volume (IRV), expiratory reserve volume (ERV), and inspiratory capacity (IC). The evaluation of respiratory muscle strength will involve assessing the maximum expiratory pressure (MEP) and maximum inspiratory pressure (MIP) using the Pony FX device (COSMED, Rome, Italy) [37].

#### 2.7.3. Physical Performance

The Functional Reach Test (FRT) will be utilized to assess physical performance [38]. The procedure will involve participants sitting upright in a wheelchair and extending both arms forward as far as possible. The initial measurement point will be the position of the fingertips when the arms are raised to shoulder height. The final measurement point will be the furthest distance reached, maintained for 3–5 s. The distance between these two points (in cm) will be recorded. An evaluator will assist from the side. Each participant will perform three attempts, and the average of these attempts will be used for analysis.

#### 2.7.4. Body Composition

Body composition will be assessed using DXA (Discovery Wi, Hologic, Marlborough, MA, USA) and bioimpedance testing (InbodyS10, Inbody, Seoul, Republic of Korea). DXA will provide extensive details on lean and fat masses for different regions of the body, whereas BIA will evaluate multiple body composition indicators, including BMI, percentage of body fat, muscle mass, and overall weight.

#### 2.7.5. Quality of Life

The World Health Organization Quality of Life (WHOQOL-BREF) questionnaire will be administered to assess the participants’ quality of life. This comprehensive assessment tool evaluates multiple dimensions of an individual’s overall well-being. The questionnaire comprises 26 items, each rated on a 5-point Likert scale. The participants will be required to rate their responses based on their experiences over the past two weeks.

### 2.8. Participant Timeline

The schedule for recruiting, conducting experiments, and evaluating study subjects is detailed in the participant timeline, as outlined by the SPIRIT guidelines in Table 3 [29].

### 2.9. Data Collection Methods and Analysis

Outcome measures will be collected before and after the 16 intervention sessions, excluding the sociodemographic and descriptive information.

The sample size determination was based on prior research findings [34]. A power analysis was conducted using G*Power software (version 3.1.2.) [39]. The analysis used an effect size of 0.5 for the outcomes, a power level of 80% (type II error of 0.2), and a significance level of 0.05. We calculated that 29 individuals per group would be required to achieve the necessary statistical power. Therefore, we plan to enroll 30 individuals per group, resulting in a total of 120 participants across the four groups. This calculation ensures sufficient power to detect meaningful differences between the intervention and control groups.

We will assess participant characteristics and baseline comparisons to assess the comparability between the exercise and control groups. A table will be provided to display the characteristics of individuals assigned by the group. Percentages and frequencies will be used to present categorical elements, and time intervals along with continuous elements will be summarized using medians, standard deviations, means, and interquartile ranges. This procedure secures the baseline equivalence between the groups.

An intention-to-treat framework will be employed for our statistical analysis. Kolmogorov–Smirnov analysis will be used to assess the normality of the dependent variables for the outcomes. The responsible variables will be characterized based on their distribution, utilizing either medians and interquartile ranges or means and standard deviations. To achieve the objective, hypothesis tests will be conducted for each outcome, positing that the exercise group will have superior outcomes compared to the control group. All estimates will be accompanied by intervals with 95% confidence level. Student’s *t*-test will be applied for independent samples that follow a normal distribution, while the Mann–Whitney U test will be utilized for data that do not conform to a normal distribution.

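### The 29 per group in section 2.9 does not follow from its stated inputs (64 per arm two-sided, 51 one-sided); the planned 60 per arm gives 77.5% power two-sided and 86% one-sided

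*Protocol article*

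**What the plan says.** Section 2.9 of the protocol article prints its inputs. The effect size is 0.5, and the rest reads "a power level of 80% (type II error of 0.2), and a significance level of 0.05". The result follows at once: "We calculated that 29 individuals per group would be required to achieve the necessary statistical power". The number is raised to 30 per group and multiplied over four groups to reach 120. The paragraph closes: "This calculation ensures sufficient power to detect meaningful differences between the intervention and control groups".

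The same section fixes the analysis. The hypothesis is directional, "positing that the exercise group will have superior outcomes compared to the control group". All estimates are to carry 95% confidence intervals. Student's t "test will be applied for independent samples that follow a normal distribution", with Mann–Whitney U otherwise. Neither the sidedness of the test nor the metric of the effect size is stated.

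Elsewhere, the Abstract assigns 120 participants to an exercise group or a control group. Section 2.1 names four hospitals. Section 2.3 randomises 1:1 within each institution. The Discussion puts each exercise group at 15 people, calls the study a pilot and warns that the small sample may limit its ability to find differences.

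**The concern.** The inputs, the result and the conclusion stand together in one paragraph, and the result does not come from the inputs. This is not a detail that the article leaves to a fuller document, because the calculation is printed and can be checked.

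The paragraph is the article's only basis for reading a null result, and the Discussion says the findings will inform later sample sizes. A reader who trusts it would take 29 per arm as enough to detect half a standard deviation. A reader who tries to work out the real power cannot, because group is not defined and the counts of 30, four, 120 and 15 are never reconciled.

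**Working it through.** **Inputs.** From section 2.9: effect size 0.5, power 0.80, alpha 0.05, independent-samples t-test. From section 2.3: 1:1 allocation. From the Abstract: 120 participants, two arms. Assumption: 0.5 is Cohen's d, the usual metric for a t-test. Sidedness is not stated, so both cases are shown.

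**1. Attempt to reproduce 29 per group.** Normal approximation: n per arm = 2(z₁ + z₂)²/d².

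- Two-sided: 2 × (1.960 + 0.842)²/0.25 = 62.8, so 63.
- One-sided: 2 × (1.645 + 0.842)²/0.25 = 49.5, so 50.

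Exact noncentral t, with df = 2n − 2 and noncentrality d√(n/2):

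- Two-sided: 63.8, so 64 per arm (128 in total).
- One-sided: 50.2, so 51 per arm (102 in total).

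The figure of 29 is not reproduced. Scaling the two-sided 64 by π/3 for Mann–Whitney on normal data gives about 67 per arm, which is further away. With 29 per arm, the effect detectable at 80% power two-sided is 0.75 SD, not 0.5.

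**2. Which n applies to the planned comparison.** 120/2 arms = 60 per arm. Spread over four sites, 120/4 = 30 per site and 30/2 = 15 per arm at each site. So 30 per group, four groups, 120 in total and 15 per exercise group agree if group means site. But section 2.9 describes the comparison as intervention against control, and no comparison within a site is planned, so a requirement of 29 per site has no test behind it.

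**3. Power at d = 0.5, alpha 0.05, exact t.** The dropout rates are assumptions; the article gives none.

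| n per arm | What it represents | Two-sided | One-sided |
|---|---|---|---|
| 29 | stated figure, if an arm | 46.5% | 59.3% |
| 30 | rounded figure, if an arm | 47.8% | 60.6% |
| 51 | 60 less 15% dropout | 70.6% | 80.6% |
| 54 | 60 less 10% dropout | 73.1% | 82.6% |
| 60 | planned 120, complete data | 77.5% | 85.9% |
| 64 | two-sided requirement | 80.1% | 87.9% |

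At 60 per arm the two-sided normal approximation gives 78.2%. Mann–Whitney on normal data, approximated as a t-test with 60 × 3/π = 57.3 per arm, gives about 75.6% two-sided. The effect detectable at 80% power with 60 per arm is 0.52 SD two-sided and 0.46 SD one-sided.

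**4. If a baseline-adjusted analysis were used.** ANCOVA divides the residual variance by 1/(1 − ρ²), so the effective effect size is d/√(1 − ρ²). The article gives no baseline correlation ρ; the values below are assumptions.

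| n per arm | ρ = 0.3 | ρ = 0.5 | ρ = 0.7 |
|---|---|---|---|
| 60 | 81% | 88% | 97% |
| 51 | 75% | 82% | 94% |

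**The case against.** The best defence is that the trial enrols 120, not 58. At 60 per arm the two-sided shortfall is 2.5 points (80 − 77.5) before dropout. The hypothesis is directional, and on a one-sided 5% test the plan exceeds 80% and still gives 80.6% after 15% dropout. All of this stands. It limits the size of the problem, but it does not rescue the 29, which is wrong under either sidedness.

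A reader might infer from the 29 or 30 per group that the trial has only 46% to 48% power. The documents do not support that. Those figures hold only if 29 or 30 is the size of a trial arm, which would make about 60 in total and contradict the 120 in both the Abstract and section 2.9.

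A reader might also take the planned test to be two-sided and call the power claim simply false. The article never says two-sided. The 95% intervals point that way, since they match a two-sided 5% test, but they do not state it.

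Finally, 29 can be reached from inputs that are not given. For example, ANCOVA with a baseline correlation near 0.74 needs about 29 per arm. But section 2.9 names no such analysis or correlation, and it plans a different test. The Discussion's caution about sample size does soften the risk of misreading a null result. It also contradicts the assurance in section 2.9.

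**Conclusion.** The concern holds in a limited form. The stated 29 per group does not follow from effect size 0.5, 80% power and alpha 0.05 for an independent-samples t-test: the requirement is 64 per arm two-sided or 51 one-sided. The assurance of sufficient power is therefore unsupported as derived, and it sits against the Discussion's own warning.

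The practical deficit at the planned enrolment is modest and depends on sidedness. Two-sided, the inputs need 128 participants with complete data against 120 enrolled. One-sided, 120 is enough. The stronger conclusion, that the trial is grossly underpowered, does not follow.

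This rests on reading 0.5 as Cohen's d, on 60 per arm from 1:1 allocation of 120, and, for the lower figures, on assumed dropout of 10% to 15%.

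**What to change.** Rewrite the sample-size paragraph in section 2.9:

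- Replace the 29-per-group sentence with the correct requirement: 64 per arm for d = 0.5, two-sided alpha 0.05 and 80% power by t-test, or 51 per arm if a one-sided test is intended.
- State the sidedness (two-sided matches the planned 95% intervals) and name the effect metric.
- Define group as arm or site, and reconcile 30 per group, four groups, 120 in total and the Discussion's 15 per exercise group.
- Restate power for the fixed 60 per arm: 77.5% two-sided with complete data, detectable effect 0.52 SD, and about 73% to 71% for assumed dropout of 10% to 15%.
- Replace the assurance of sufficient power with these figures, and make the Discussion's limitation agree with them.

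A baseline-adjusted ANCOVA is an option, not a requirement. If it is adopted, report power over a range of assumed baseline correlations, because 51 per arm at a correlation of 0.3 would still be below 80%.

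The cost is one paragraph and one sentence in the Discussion. The stated two-sided power becomes slightly less favourable. No extra enrolment is asked for.
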